### Interrupted Time Series: Study Design

Following the completion of the pilot stage, the team will conduct an interrupted time series study featuring quasi-experimental pilot effectiveness research methods to evaluate the Fam-AID protocol and implementation toolkit [87]. Figure 2 depicts the basic design and timeline of the interrupted times series study. The quasi-experimental interrupted time series with nonequivalent groups, which tracks target data both before and after introducing a programmatic change to a group whose membership may vary over time, is appropriate for testing viability and impacts of new interventions delivered in field settings [88-90]. This design is functionally similar to a posttest-only design with a nonequivalent historical control group. Two partner clinic sites will be involved to reduce confounds from site-specific implementation effects and increase diversity in clients and therapists. Aim 1 methods will feature procedures designed for stage 1 treatment development [91,92] to establish proof-of-concept (acceptability and fidelity benchmarks) for the protocol and toolkit. Aim 2 methods will examine Fam-AID’s impact on family member attendance in treatment and client outcomes (adolescent ID symptoms, adolescent SU, and parent-adolescent communication about SUD+ID).

**Figure 2 figure2:**
[figure not shown]
Design and timeline of study activities for this study. TAU: treatment as usual.

### Study Sites and Participants

Both study sites are licensed to deliver SUD services to adolescents. Neither site currently supports an evidence-based treatment protocol that specifically targets IDs. Participant inclusion and exclusion criteria are shown in Textbox 1.

Participant inclusion and exclusion criteria.
**Inclusion criteria**
The adolescent is aged 13 to 18 years.The adolescent lives with a primary caregiver who can attend treatment sessions.The adolescent endorses ≥1 *Diagnostic and Statistical Manual of Mental Disorders, Fifth Edition, Text Revision* [93] symptom for substance use disorder and meets the American Society of Addiction Medicine criteria for outpatient substance use treatment.The adolescent meets the *Diagnostic and Statistical Manual of Mental Disorders, Fifth Edition, Text Revision* criteria, or has elevated symptoms and impairment, for an ID, with the following expected to be most common: current or recurrent major depressive episode, pervasive depressive disorder, social anxiety disorder, generalized anxiety disorder, panic disorder, and posttraumatic stress disorder.The adolescent completes intake and is enrolled as an active case at the study site.
**Exclusion criteria**
The adolescent has an illness requiring hospitalization.The adolescent has current psychotic symptoms.The adolescent has severe substance use problems that require immediate relief (detox or residential placement).The adolescent has pervasive developmental disorder.

To match real-world care, no eligibility criteria or other study directives will pertain to medication status. Assessment data collected during previous studies in the same regions [79,94] provide the following adolescent demographic projections: average age approximately 16 years; male participants, 70% (42/60) and female participants, 30% (18/60); Black, 15% (9/60); Latinx, 40% (24/60); White non-Latinx, 40% (24/60); and other, 5% (3/60).

### Study Condition: TAU Only

Previous research on TAU intervention delivery at both study sites using therapist self-report [95] and observational data from session recordings [96] indicates that site therapists routinely deliver relatively low-dose quantities of evidence-based SUD treatment techniques, favoring motivational interviewing and addiction counseling techniques, with even less delivery of CBT or family therapy techniques for SUD. Sites do not have existing protocols for treating IDs as either main referral problems or cooccurring conditions.

### Study Condition: TAU+Fam-AID

#### Overview

Fam-AID will contain 5 modular components to be delivered in any order and to the extent indicated based on case status [37,43,97]. Modules can be individually or collectively completed in 1 session, staggered across sessions, and interspersed with other interventions. The time required to complete each module will vary based on client profile, practice habits of the provider, and case progress. Fam-AID will have standardized options for versatile delivery with individual adolescents alone whenever family members cannot be engaged in services; modules 3 and 4 can proceed intact, and module 5 can be adjusted for adolescent-only delivery. The study will be halted if it appears that Fam-AID delivery induces clinical harm. The following is a description of the projected module content, considering that the ultimate set of modules and their content will be determined over the course of the study:

#### Module 1: Culturally Attuned Family Engagement

To promote family engagement, clinicians collaborate with the family members by instilling hope and involving them in goals related to ID problems. They encourage the family members to attend sessions throughout care, present treatment as an opportunity to talk about new issues or old issues in new ways, connect with the family members by showing respect and validation, and use relevant self-disclosure to establish connections [98-100]. Family engagement is guided by the principles of cultural attunement [101], which include accentuating values and strengths minimized in dominant culture, remaining accountable for how interventions disrupt or reinforce existing inequities, and encouraging the family members to make conscious choices about how they frame their identities and respond to injustice.

#### Module 2: Relational Reframing of ID Symptoms

Clinicians use relational reframing techniques to shift the focus of treatment from exclusively fixing adolescents and their symptoms to improving the quality of adolescent-family relations. They assert that treatment should be grounded in acknowledging, understanding, and repairing relationship problems as a means of addressing adolescent ID problems and bolstering individual and family recovery paths. Basic approaches to delivering a relational reframe for adolescent IDs include identifying sequences of behaviors or emotions involving families that precede or directly cause identified problems; focusing on the impact that ID-related problems have on the thoughts, feelings, and behaviors of both adolescent and family; and supporting relational repair or improvement [52-55].

#### Module 3: Functional Analysis of ID Symptoms

Clinicians use functional analysis to uncover information about reinforcers of symptoms to render interventions that are personally relevant as well as help adolescents and families understand behavioral chains of antecedents and consequences that maintain problems. Functional analysis steps for adolescent ID include [102-104] articulating scenarios in which ID-related problems occur; examining circumstances that precede problems, ascertaining both internal and external antecedents; identifying short-term positive outcomes and long-term negative outcomes; and engaging clients in comparing positive versus negative consequences. Clinicians are careful to validate feelings that emerge, reflect appreciation for client sharing, and maintain a stance of curiosity about the perceived value of behaviors and an empathic position in exploring healthier alternatives.

#### Module 4: CBT Treatment Techniques for ID

Clinicians use data from the functional analysis of ID symptoms to choose from a selection of 3 transdiagnostic CBT techniques that have evidence for treating both depression and anxiety in teens [105,106]. In *emotional acceptance*, adolescents develop skills for noticing and accepting their emotions, including unpleasant and strong emotions [60,61,64,68], which help reduce anxiety sensitivity. They learn skills of present-moment and nonjudgmental awareness, which can increase affect tolerance [107]. In both *emotional exposure* and *behavioral activation*, adolescents are helped to approach situations, thoughts, and triggers that elicit strong emotions that have been previously avoided [60,61,64,102,104,108,109]. They try out various “opposite” actions to their typical emotional responses or behaviors (eg, volunteering to speak in class) to increase distress tolerance. Adolescents are encouraged to use new skills to fully engage in situations eliciting strong emotions and maintain clarity about the purpose of the opposite actions they select. All 3 techniques operate primarily on an approach versus avoidance clinical mechanism.

#### Module 5: SUD+ID Education and Safety Planning

Clinicians use family decision coaching [79,110,111] to converse with family members about three overlapping pathways of SUD and ID cooccurrence [10,112-114]: (1) self-medication: ID precedes the onset of SUD, and substances are valued for psychoactive properties that alleviate ID symptoms; (2) SU exposure: SUD precedes the onset of ID and creates developmental lag in the emergence of self-regulatory functions that precipitate ID and, if severe, impair neurocognitive functioning; (3) shared etiology: SUD and ID are mutually influencing axes of dysregulation that compromise healthy development. Family SUD+ID education transitions to family-based safety planning about both nonsuicidal self-injury and suicide ideation and attempts, guidelines for which focus on establishing physical and psychological safety, identifying strategies that can be used instead of self-harm, and identifying individuals to whom the adolescent can go for help [73,74,115,116].

### Fam-AID Training and Fidelity Monitoring

Site clinicians will be trained for 6 hours. The session will feature video-based training [117,118] in Fam-AID modules and techniques. Thereafter, consultation at each site will include bimonthly live consultation with a protocol expert focused on equipoise between protocol fidelity and case tailoring, along with continuous feedback from therapist- and observer-report fidelity data, which is emailed directly to clinicians and used in live consultation to enable rapid adjustment in protocol delivery [119-121]. Two main fidelity benchmarks will be monitored for each case. These benchmarks include clinicians delivering interventions for every module in at least 1 treatment session (ie, coverage) and clinicians performing at or above the mean scale score for intervention extensiveness on the Fam-AID Fidelity Checklist (described in the Study Measures section) for at least 1 technique from each module (ie, dose), with both therapist- and observer-report checklist versions being tracked.

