### Specific Aims of the Study

In year 1, this study will develop a Fam-AID implementation toolkit during a three-part *pilot stage* at 1 pilot site by (1) soliciting provider input on Fam-AID components; (2) creating video-based training and fidelity procedures, leveraging the research team’s existing training and consultation resources in both core family-based interventions [75,76] and adolescent-focused transdiagnostic techniques [77] for adolescent behavior problems; and (3) piloting the toolkit with 4 to 6 clients. In years 2 to 3, this study will conduct an *interrupted time series* evaluation for 60 adolescent SUD+ID cases across 2 sites serving diverse clients: 30 cases will receive treatment as usual (TAU), and then following clinician training, 30 new cases will receive TAU enhanced by Fam-AID.

This protocol development study has 2 specific aims:

Aim 1 (protocol feasibility): in the Fam-AID condition only, the study will evaluate (1) protocol acceptability via client and therapist qualitative interviews and (2) fidelity benchmarks via therapist- and observer-report fidelity measures of protocol coverage (Is each module delivered in at least 1 session?) and protocol dose (Is the average module extensiveness score greater than the mean of the fidelity measure?).Aim 2 (protocol outcomes): in comparing the TAU only condition versus the TAU+Fam-AID condition, the study will examine the protocol’s impacts on (1) family member session attendance using clinic logs and (2) adolescent ID-related symptoms (emotion regulation, depression, and anxiety), SU, and family communication about SUD+ID at 3-month and 6-month follow-up. Overall, these pilot-scale protocol viability and impact findings, if promising, will set the stage for a randomized trial to examine the effects of Fam-AID on immediate and ultimate outcomes in a larger community sample.

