Clinicians in both conditions will be asked to complete a self-report fidelity measure after every session with a study client. They will also be asked to audio record all sessions, a minimally intrusive procedure that is widely accepted by families and therapists in previous work [94]. Data will be collected using web-based links and uploaded to secure servers. As per the study team’s numerous observational fidelity studies [126-130], 1 session will be randomly selected from the early phase of treatment (sessions 1 to 3) and 2 from the later phase (sessions from session 5) of each client for coding with an observational version of the Fam-AID Fidelity Checklist (described in the Study Measures section). Fidelity observational coders will be trained by the study team using gold standard procedures [126,131-133] and kept naive to the study condition.

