### Study Measures

#### Fam-AID Fidelity Checklist

This study will use an adapted version of the Inventory of Therapy Techniques (ITT [95,96]), a postsession therapist-report fidelity tool that requires 1 or 2 minutes to complete. ITT items are designed to measure the extensiveness (ie, thoroughness and frequency) with which a given treatment technique was used on a 3-point Likert-type scale: 0 (not at all), 1 (a little bit or moderately), or 2 (quite a bit or extensively). ITT items are derived from treatment protocols and their associated observational fidelity tools, for example, for family therapy [51] and for CBT [67], after being vetted for relevance by community clinicians in multiple treatment settings [134]. ITT has shown strong construct [50,134] and predictive [79,135] validity in studies with adolescents receiving family therapy and CBT in usual care. The Fam-AID Fidelity Checklist mimics the ITT structure, containing multiple items in each of the 5 Fam-AID modules: culturally attuned family engagement, relational reframing of ID symptoms, functional analysis of ID symptoms, CBT treatment techniques for ID, and SUD+ID education and safety planning. The Fam-AID Fidelity Checklist–Observer Version is an identical measure with instructions for observer coding.

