*Aim 1 fidelity benchmarks* analyses (Fam-AID condition only) will examine both types of previously described fidelity metrics. Regarding coverage, descriptive statistics will capture frequencies related to (1) proportion of clients who received at least 1 intervention from each of the 5 modules and (2) interventions from which modules were most or least favored across clients. Chi-square analysis will be used to compare study conditions on the proportion of clients who received adequate coverage and conduct one-way analysis of variance to assess mean differences across modules in the Fam-AID condition to evaluate module preferences among therapists. Regarding dose, statistical equivalence testing [153] will be used to examine whether clinicians’ average scores for intervention extensiveness on both observer- and therapist-report versions of the Fam-AID Fidelity Checklist are equivalent to a designated benchmark, which will be set (granting appropriate latitude for a pilot trial) for each module as mean 2.5 (SD 0.50). A CI approach will be adopted in which an equivalence interval is defined as the benchmark +10% and –10%. Next, a CI is defined by the following formula: CI_90%_=M_R_–M_T_+/–z_α_(S_MR−MT_). In this equation MR represents the benchmark module mean, MT the average module score for study therapists, zα the critical one-tailed value from the z distribution for the chosen value of α, and SMR−MT the pooled SE. If the calculated CI falls within the equivalence interval, equivalence can be concluded. In addition, therapist variability in Fam-AID fidelity will be examined via statistical process control analyses (refer to the study by Hogue and Dauber [125]) in which individual therapist fidelity scores are plotted on a control chart to check for meaningful variation compared to control limits represented by the designated fidelity benchmark.

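### The fidelity dose benchmark has three incompatible definitions: one can collapse into coverage on a 0/1/2 scale, and another lies above the scale maximum

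*Protocol article*

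**What the plan says.** All references are to the Protocol article.

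- **Scale.** Fam-AID Fidelity Checklist describes the parent instrument's ratings as "0 (not at all), 1 (a little bit or moderately), or 2 (quite a bit or extensively". It adds: "The Fam-AID Fidelity Checklist mimics the ITT structure, containing multiple items in each of the 5 Fam-AID modules".
- **Per-case monitoring.** Fam-AID Training and Fidelity Monitoring names two main benchmarks. The first is "clinicians delivering interventions for every module in at least 1 treatment session (ie, coverage". The second is "clinicians performing at or above the mean scale score for intervention extensiveness on the Fam-AID Fidelity Checklist", to be met "for at least 1 technique from each module (ie, dose". The section does not say whether the mean scale score is the scale midpoint or an observed mean. Nor does it say whether a technique's score is its best session or its average over sessions.
- **Aims.** Specific Aims of the Study puts the dose question as: "Is the average module extensiveness score greater than the mean of the fidelity measure".
- **Analysis.** Plan of Analyses tests dose by equivalence. The benchmark is set "for each module as mean 2.5 (SD 0.50", with an equivalence interval of 10% either side.
- **Data available.** Study Procedures states: "Clinicians in both conditions will be asked to complete a self-report fidelity measure after every session with a study client". Observers code three sessions per client, one early and two later.

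**The concern.** Coverage and dose are presented as separate benchmarks, so dose should say something that coverage does not. On a three-point item the midpoint is also the lowest non-zero score. A rule of the form 'at or above the midpoint, for at least one technique' can therefore be met by the weakest delivery the checklist records.

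The other two sections state different rules. One uses a module average and a strict inequality. The other uses a numeric target above the top of the scale. The same fidelity data could then be reported as near-universal success, partial success or certain failure, depending on which section is followed.

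This matters because fidelity benchmarks are part of the proof of concept that the design section asks Aim 1 to provide, and the findings are meant to support a later randomized trial. The per-case benchmarks are also monitored during delivery, alongside fidelity feedback to clinicians, so an unclear rule affects more than the final report.

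**Working it through.** The monitoring section gives no number to reproduce. The check is to apply each stated rule to the stated scale.

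**1. Scale.** Midpoint = (0 + 1 + 2)/3 = 1. Lowest non-zero rating = 1. Maximum = 2.

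**2. Literal monitoring rule.** Ratings are whole numbers, so a rating of at least 1 and a rating above 0 are the same event. If one session rating of one technique is enough, dose is met exactly when coverage is met.

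**3. Comparing the readings.** Assume, for illustration, one module with 2 techniques rated in 3 sessions. There are 3^6 = 729 rating patterns, weighted equally. The counts show how far the rules differ; they do not predict attainment. Coverage (any rating above 0) is met in 729 − 1 = 728.

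| Dose rule | Met | Disagrees with coverage |
|---|---|---|
| Any single rating at or above 1 (literal monitoring rule) | 728 | 0 |
| A technique's average over sessions at or above 1 | 629 | 99 |
| Any single rating at or above an observed mean above 1 (1.2 assumed) | 665 | 63 |
| Module average strictly above 1 (aims rule, mean taken as midpoint) | 294 | 434 |

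Derivations:
- Technique average: of a technique's 27 patterns, 7 sum to exactly 3, and (27 − 7)/2 = 10 fall below. Both techniques fail in 10 × 10 = 100 patterns, and 729 − 100 = 629.
- Observed mean of 1.2: a rating of 2 is needed, so 729 − 2^6 = 665.
- Module average: 141 patterns sum to exactly 6, and (729 − 141)/2 = 294.

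**4. Averaging and the modular design.** The TAU+Fam-AID overview lets a module be completed in one session. Averaged over all sessions, a technique rated 2 once scores 2/3 = 0.67 over three sessions and 2/10 = 0.2 over ten. Both miss a threshold of 1 although delivery was at the top rating. The Discussion also lets client and therapist choose among the three CBT techniques in module 4. Assuming one item per technique, using one at level 2 and the others not at all gives a module average of (2 + 0 + 0)/3 = 0.67.

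**5. Analysis benchmark.** 2.5 × 0.9 = 2.25 and 2.5 × 1.1 = 2.75. A mean of 0 to 2 ratings cannot exceed 2. The plan's formula works on the difference between benchmark and therapist mean. That difference is at least 2.5 − 2 = 0.5, while the margin on the same scale is 2.5 × 0.10 = 0.25. An interval centred at 0.5 or more cannot lie within ±0.25, so equivalence cannot be concluded.

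**The case against.** A reader might infer that dose and coverage always give the same answer and that the protocol therefore measures no dose. The documents do not support that.

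- The identity needs two readings that the monitoring section leaves open: a cut-off no higher than 1, and a single session rating being enough. Therapists rate every session, so averaging is a natural alternative, and it separates the benchmarks in 99 of 729 patterns. An observed mean above 1 also separates them. Finding no disagreement under the literal reading follows from the definition and is not empirical evidence.
- The aims and the analysis section both work with averages. One minimal rating satisfies neither. The analysis section also reports coverage separately, as a proportion of clients. The redundancy is confined to the monitoring benchmark.
- A reader might also take the strict inequality in the aims to demand the top category. It applies to a module average: ratings of 2, 1 and 1 average 1.33 and pass.

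These limits stand. They do not remove the point. The literal reading is the plainest one, since no averaging is mentioned there. Averaging over all sessions counts against delivery that the modular design allows. An observed mean would move with the study's own data. None of these readings reconciles the three sections. Nor is this detail left to a fuller plan: the article states all three rules, and they conflict.

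**Conclusion.** The point holds as an inconsistency in the definition of dose. Read literally, the monitoring rule adds nothing to coverage (728 of 729 patterns met by each, none discordant). The aims rule differs sharply from it (294 of 729). The analysis benchmark of 2.5 is unreachable by at least 0.5 scale points.

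The first result assumes that the mean scale score is the midpoint and that any one session rating counts. The second takes the mean in the aims as the midpoint and rests on an illustrative module of 2 techniques and 3 sessions with equal weights. The third needs only that the checklist keeps the 0 to 2 scoring and that module scores are averages, as the article describes. The article should be corrected before fidelity data are collected, because the choice of rule decides what Aim 1 can conclude about dose.

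**What to change.** Use one dose definition in Specific Aims of the Study, Fam-AID Training and Fidelity Monitoring, and Plan of Analyses. It should state:

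1. the unit (single technique or module average);
2. the aggregation over sessions, for both the therapist and the observer version;
3. a numeric threshold within 0 to 2 that a single rating of 1 does not automatically meet, in place of the undefined mean scale score and of 2.5, with the equivalence interval recalculated from it.

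Keep coverage as any rating of 1 or more.

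One candidate is the aims rule made explicit: a module average strictly above 1, taken over the sessions in which the module was delivered. In the illustration above it is met in 381 of 729 patterns. (A delivered session's total minus 2 is −1, 0, +1 or +2 in 2, 3, 2 and 1 ways; an undelivered session adds 0 in 1 way; three sessions sum above 0 in 381 patterns.) It removes the penalty for completing a module in one session. The team must still decide how techniques deliberately not chosen, as in module 4, enter the average.

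Simply requiring one technique rated 2 in one session would not reconcile the sections. It passes 665 patterns against 294 for the aims rule. Every pattern averaging above 1 contains a 2, so the two disagree on 665 − 294 = 371. It also leaves the 2.5 untouched.

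The cost is a wording change with no new data. Under the candidate rule dose attainment cannot exceed coverage and will probably be lower.
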